### **10.3 Tumor markers**

According to the results of follow-up, the changes of tumor markers will be evaluated.

### **10.4 Objective evaluation of efficacy**

According to the results of B ultrasound, CT or enhanced MR, chest CT and other imaging studies, recurrence would be assessed.

## **11. Safety evaluation**

From the beginning of that patients signed the informed consent and are selected for trial to one month after the end of treatment, any adverse medical events, regardless of whether a causal relationship with the study medication, will be judged to be Adverse Event (AE).

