## 4.2 Population and Period

The total number of cases is 68.

It was reported that the median tumor-free survival time or median recurrence time was 13-24 months after a curative surgery for HCC. In this study, the median recurrence time of the control group is supposed to be 18 months. That of the group of patients with implantation of  $^{125}\text{I}$  is expected to be 36 months (the hazard ratio of  $^{125}\text{I}$  was 0.5). A probability value of  $<0.05$  in one-sided test is considered statistically significant. Power of the test was 0.80. The number of cases in the study is 68.

These patients will be treated in our hospital from July 2000 to June 2004. The follow-up period was extended to 5 years after surgery.

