## 5. Method

### 5.1 Radionuclides

#### 5.1.1 $^{125}I$

$^{125}I$  is produced in Reactor Engineering Research of China Institute of Atomic Energy with 0.8mm  $\times$  4.5mm and a half-life of 59.6 days and enveloped with Nickel titanium alloy. It is sterilized under high temperature. It has X-ray with energy of 27.4-31.5Kev and  $\gamma$ -ray with energy of 35.5

Kev. The activity of per seed is 0.5-0.6mCi.

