### **5.2.2 Interventions of two groups after removal of the tumor**

I group: The wound will be carefully stanch after the tumor has been removed completely. The square meter of the wound will be measured and the data will be input into the computer to determine the number of radionuclides implanted and doses. Mick radionuclide applicator will be used to implant I at 1cm interval in the normal liver tissues at the incisional margin (I was produced in Reactor Engineering Research of China Institute of Atomic Energy with 0.8mm×4.5mm and a half-life of 59.6 days and enveloped with Nickel titanium alloy. It is sterilized under high temperature. It has X-ray with energy of 27.4-31.5Kev and γ-ray with energy of 35.5 Kev. The activity of per seed is 0.5-0.6mCi. The prescription dose was 160Gy). Ultrasonography is utilized to see whether seeds are well-distributed. More seeds will be implanted so as to avoid cold spot areas if seeds are not well-distributed. Fibrin gel will be smeared on wounds and then sutured with absorbable gelatin sponge or hemostatic gauze to prevent I from dropping off. The rest treatment of the control group is the same as that of the I treated group except for implantation of I. Both of the groups will receive identical routine support treatment for the liver after surgeries.

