## **9. Follow-up**

Patients must be arranged for close follow-up which included rechecks every 2-3 months or contact by phone after entering the treatment group.

Follow-up will be carried out according to the following stipulations with CRF filling:

Every 2 to 3 months: blood routine, liver and kidney function, AFP, liver ultrasonography;

Every 3 to 4 months: enhanced abdominal CT or MRI.

Every six months: chest X-ray or chest CT;

If the patient had signs of distant metastases of the lung, bone, intracranial, whole-body bone scan, CT of other parts, and even PET-CT should be added.

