### **11.3 Serious adverse event (SAE)**

The judgments of SAE:

- Death;
- Life-threatening;
- Leading to hospitalization or prolong hospitalization time;
- Permanent or severe disability.

SAE report system:

The person in charge in the unit and the hospital ethics committee should be reported and SAE report form should be filled in within 24 hours by phone no matter whether any kinds of SAE are related with the drug in 30 days after the treatment. And the form should be reported to national drug administration in time by the person in charge. SAE should be promptly handled, closely tracked until it is properly solved.

Contact method:

- 1) Contact persons: [name] [name]    [name] [name]
- 2) SFDA Safety Supervision

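### Collection of new AEs and SAEs closes about a month after an undefined end of treatment; counted from surgery, about 70% of the 125I decay is still to come

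*Protocol*

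**What the plan says.** Section 11 (Safety evaluation) treats any untoward medical event as an AE, whatever its cause, from consent "to one month after the end of treatment". Section 11.3 sets a matching limit for serious events, which are to be reported "no matter whether any kinds of SAE are related with the drug in 30 days after the treatment".

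The experimental treatment is a single intraoperative implantation. Section 5.1.1 describes seeds with "a half-life of 59.6 days". Section 5.2.2 adds "The prescription dose was 160Gy" and has the wound covered "to prevent 125 I from dropping off". No section describes taking the seeds out.

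Section 11.2 has AEs followed until they resolve or stabilise, and SAEs followed even beyond the end of the study. Section 9 schedules "Every 2 to 3 months: blood routine, liver and kidney function, AFP, liver ultrasonography", with enhanced CT or MRI every 3 to 4 months and CRF entry. On duration, section 4.2 says: "The follow-up period was extended to 5 years after surgery". Section 2 places safety beside efficacy in Objective 1.

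**The concern.** A window of about a month after treatment suits a drug whose exposure stops with the last dose. Here the source stays in the liver and goes on irradiating for months. The protocol does not say when treatment ends for such a source. The natural reading is the operation, because that is the only treatment act described.

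On that reading, collection of new events stops while most of the irradiation is still to come. Both arms have the same hepatectomy, so the first month will include surgical events common to both. A clinical effect of the implant that first appeared later would not be an AE by definition, and a non-fatal serious one would carry no reporting duty. Section 1.2 says there have been no earlier studies of 125I for this use, so the trial cannot lean on existing safety data. If late effects occur, the comparison would understate them.

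**Working it through.** **Inputs.** Half-life 59.6 days (5.1.1). Collection closes one month or 30 days after treatment (11, 11.3). Prescription dose 160 Gy (5.2.2). Contacts every 2 to 3 months (9). Median time to recurrence 18 months in controls and 36 months with 125I (4.2). The protocol states no delivered fraction, so there is no figure of its own to reproduce.

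**Assumptions.** Treatment ends on the day of surgery; the seeds stay in place; dose is proportional to decay. The gray figures also assume that 160 Gy is the dose to complete decay, which the protocol does not say.

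**Step 1: fraction delivered by day t** = 1 − 2^(−t/59.6).

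| Day | Fraction delivered |
|---|---|
| 7 | 7.8% |
| 30 | 29.5% |
| 60 | 50.2% |
| 90 | 64.9% |
| 180 | 87.7% |
| 365 | 98.6% |

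For day 30: 30/59.6 = 0.503 and 2^(−0.503) = 0.705, so 29.5% is delivered and 70.5% remains. With a month of 28 to 31 days, the delivered fraction is 27.8% to 30.3%. In dose terms, 0.2945 × 160 = 47.1 Gy falls inside the window and 112.9 Gy after it.

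**Step 2: when irradiation is largely over.** Solving for t, 90% is reached at about day 198 and 95% at about day 258.

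**Step 3: tests inside the window.** Section 4.3 schedules blood on the day before surgery and on day 7. Section 8.1 adds baseline tests. The next scheduled blood counts and liver and kidney tests come at 2 to 3 months, after closure. Day 7 is thus the only scheduled post-operative draw in the window.

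**Step 4: the other reading of the end of treatment.** Suppose it meant the point where 95% of decay is complete, about day 258. A further 30 days leaves 0.05 × 0.705 = 3.5%, so the window would cover 96.5% of the dose. The undefined term therefore moves coverage between about 29% and nearly all of it.

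**Step 5: a side effect of a longer window.** With exponential recurrence times and the medians in 4.2, recurrence by 12 months is 1 − 2^(−12/18) = 37% in controls and 1 − 2^(−12/36) = 21% with 125I. Hospital stays for recurrence count as SAEs under 11.3, so all-cause SAEs would differ by arm through efficacy alone.

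**The case against.** The strongest reply is that late safety data are not lost. Blood counts, liver and kidney function and imaging continue in both arms with CRF entry, follow-up runs for 5 years, and deaths enter overall survival. How the laboratory data are summarised may well be left to a statistical analysis plan, which is not shown. This stands, and it narrows the gap to late-onset, non-fatal clinical events and to the status of late laboratory and imaging abnormalities, which are recorded but not counted as AEs.

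A second reply is that section 11.2 has AEs recorded during the trial and followed to resolution, which might be read as covering the whole study. It does not fill the gap. Section 11 defines which events count as AEs, and 11.2 governs how those events are recorded and followed. It does not bring in events that begin later.

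A third is that the end of treatment might mean the end of effective irradiation. The text does not exclude this, but section 11.3 counts simply from the treatment. If the term can be read both ways, it needs defining.

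Three stronger readings are tempting and should not be drawn:

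- **That most radiation toxicity falls outside the window.** The calculation concerns dose. The documents give no data on when toxicity appears.
- **That controls have no end date.** They have the same hepatectomy, which section 5.2 lists under treatment, so if the operation ends treatment the date is the same in both arms.
- **That day 7 is the only blood draw in the window.** The window opens at consent, so the pre-operative draws fall inside it too.

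**Conclusion.** The point holds in a limited form. The protocol closes collection of new AEs and SAEs about a month after an end of treatment that it does not define for a permanent implant. If that end is the operation, about 29% of the decay (27.8% to 30.3%) is complete at closure. About 70% of the dose, and any non-fatal clinical event first appearing after day 30, falls outside collection.

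The percentages rest on the protocol's half-life and on seeds that stay in place; the gray figures need the further assumption about 160 Gy. Any bias towards finding no added toxicity is conditional on late effects occurring, and its size cannot be derived from the document. Time to recurrence and overall survival are not affected. What is weakened is the safety half of Objective 1.

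**What to change.** In sections 11 and 11.3, define one window for both arms, counted from the date of surgery, and reconcile it with the half-life in 5.1.1 and the schedule in section 9. Collect new AEs and SAEs at the existing 2 to 3 monthly contacts over the period of meaningful irradiation. Twelve months is an example that covers 98.6% of decay; the exact length is a judgement for the sponsor.

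Grade the scheduled blood counts and liver function tests at those contacts and report them by arm. Record events due to recurrence or its treatment in a separate category, with the attribution rule written down in advance, so that the recurrence difference in step 5 does not appear as a safety difference.

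The cost is revised wording, an AE page for contacts that already take place and some extra reporting, with no new visits or tests. The work is more than a form, because section 9 allows telephone contact and section 8.2 allows examinations at local hospitals, so AE questions need to be asked the same way in those settings.

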### **11.1 Judging criteria of AE and its degree:**

We follow NCI-CTC grading criteria (Canada National Cancer Institute with expanding common toxicity criteria by CTC) for AE and its degree judgment. For those adverse reactions that are not listed in the NCI-CTC, we intend to classify the degree as follows:

Mild: patients are easier to accept without induced questions, or patients have only mild discomfort which does not affect their daily lives and there is no need for clinical treatment.

Moderate: patients actively describe the symptoms that affect the life, but they can tolerate, which needs normal clinical treatment.

Severe: patients have objective manifestations, which significantly affect the life, and patients cannot bear to stay in bed, which needs active clinical treatment.

### **11.2 Records and follow-up of AE**

During the test, AE will be accurately recorded, including the time of occurrence, severity,

duration, the measures taken and the outcome. Researchers will follow all the AE until the symptoms of patients disappeared or condition become stable. SAE should be tracked until a proper solution is found even though the study is over.

### **11.3 Serious adverse event (SAE)**

The judgments of SAE:

- Death;
- Life-threatening;
- Leading to hospitalization or prolong hospitalization time;
- Permanent or severe disability.

SAE report system:

The person in charge in the unit and the hospital ethics committee should be reported and SAE report form should be filled in within 24 hours by phone no matter whether any kinds of SAE are related with the drug in 30 days after the treatment. And the form should be reported to national drug administration in time by the person in charge. SAE should be promptly handled, closely tracked until it is properly solved.

Contact method:

- 1) Contact persons: [name] [name]    [name] [name]
- 2) SFDA Safety Supervision

## **12. Quality assurance**

In order to ensure that the experiment could be carried out in strict accordance with the clinical research program, the whole process of clinical trials should be strictly in accordance with requirements of Good Clinical Practice (GCP) issued by National SFDA, which need the researchers ensure the right of patients with standardized test procedures, accurate data, reliable results and credible conclusions. The specific requirements are as follows:

### **12.1 Requirements of researchers**

- Medical staffs who participated in the trial should be organized to systematically study and be seriously familiar with the research program before the study.
- To make sure that all the study procedures are carried out in accordance with the unified program;
- Researchers should talk to the enrolled patients or their designated agents before they signed "informed consent";
- The study should be carried out in strict accordance with the uniform requirements, and Case Report Form (CRF) should be filled in seriously;
- Clinical inspectors should regularly have follow-up;
- Clinical records, the original medical records of the subjects and laboratory records should be completely reserved.

### **12.2 Requirements of inspectors**

Specialized inspectors are selected in order to be in accordance with GCP requirements issued by SFDA in the trial.

- The inspectors should check the subjects' informed consents and situation of screening regularly in the process;
- All CRF should be confirmed to filled in correctly and were consistent with the original data;
- All errors or omissions had been corrected or annotated, which were dated and signed by the

researchers;

- Each subject should be identified and recorded;
- Verification of the exit and lost of the selected subjects should be described in CRF;
- To make sure that all adverse events had been documented, serious adverse events had been reported and recorded;
- Test supplies should be confirmed whether they were supplied, stored, distributed and recovered in accordance with the relevant provisions and appropriate record should be made;
- Each selected patient must complete CRF. The completed original CRF belonged to Second People's Hospital in Guangdong Province, which should not be provided to third parties in any form without the written consent, unless national SFDA.

### **13. Data analysis and retention**

#### **13.1 Case Report Form (CRF)**

CRF should be filled in promptly with accuracy by the researchers. CRF should not be altered generally. If there is an error that is needed to be modified, you should sign the place that is modified (CRF filling instructions). CRF is triplicate. After the completed reports are reviewed by Clinical Research Associate (CRA), data are recorded and uploaded. At the same time, the content of CRF can not be modified.

#### **13.2 Statistical analysis**

Professional statistical workers will undertake statistical analysis tasks, and participated in the whole process from experimental design and implementation to analysis and summarization. After the completion of the trial protocol and CRF, the development of statistical analysis plan is formulated, and the statistical analysis report will be provided after the necessary changes in the analysis during the testing process.

Statistical methods: the statistical quantitative index include mean, standard deviation, median, minimum, maximum. All statistical tests use two-sided test,  $P \leq 0.05$  is considered to have statistically significant difference. The comparison among enumeration data use  $\chi^2$  test. The inter-group comparison of measurement data took use of t test after normal step test and homogeneity test for variance. We use life table for the estimation of survival rate, Log-rank test for the comparison of survival rate among groups and Kaplan-Meier method for survival curves. COX regression analysis will be for the relevant factors affecting patients' survival.

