## 4.3 Grouping

All of the patients will be grouped after receiving curative surgeries for HCC.

$^{125}\text{I}$  treated group: The wound will carefully stanch after the tumor have been removed completely. The square meter of the wound will be measured and the data will be input into the computer to determine the number of radionuclides will implant and doses. Mick radionuclide applicator will be used to implant  $^{125}\text{I}$  at 1cm interval in the normal liver tissues at the incisional margin ( $^{125}\text{I}$  was produced in Reactor Engineering Research of China Institute of Atomic Energy with  $0.8\text{mm} \times 4.5\text{mm}$  and a half-life of 59.6 days and enveloped with Nickel titanium alloy. It is sterilized under high temperature. It has X-ray with energy of 27.4-31.5Kev and  $\gamma$ -ray with energy of 35.5 Kev. The activity of per seed is 0.5-0.6mCi). Ultrasonography is utilized to see whether seeds are well-distributed. More seeds will be implanted so as to avoid cold spot areas if seeds are not well-distributed. Fibrin gel will be smeared on wounds and then sutured with absorbable gelatin sponge or hemostatic gauze to prevent  $^{125}\text{I}$  from dropping off.

Control group: The rest treatment will be the same as that of the  $^{125}\text{I}$  treated group except for implantation of  $^{125}\text{I}$ .

Both of the groups received identical routine support treatment for the liver after surgery.

All of the patients will receive venous blood collection on one day before surgeries and day 7 after surgery. Aminotransferase and bilirubin were measured. AFP and MMP-9 will be measured via radioimmunoassay. Meanwhile, activity of nature killer cells and T cell subsets will be measured by flow cytometers (America COULTER). Curative hepatectomy of HCC must meet these following conditions: a. Tumor is completely removed. Explorations during surgery show no tumor remaining and fast pathology results revealed that there are no cancer cells in the incisional margins. b. There are no macroscopic cancer emboli in the main side branches and bile duct bifurcations. c. The number of the tumor is less than three. d. There is no extrahepatic metastasis.

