## **8. Observed indicators and inspection time**

### **8.1 Examinations before entering the groups**

- Physical examination, vital signs and physical status score;
- Blood routine, liver and renal function;
- Hepatitis virus;
- ECG;
- Imaging studies: (B ultrasound must be carried out; enhanced abdominal CT or MRI was needed) In order to reduce the detection error, the method of examination of the tumor lesion hospitals and the equipments for use must be consistent;
- Serum tumor markers: AFP, CEA, and CA199.

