## **10 Clinical evaluations: the judgment of efficacy is mainly based on the following indicators**

### **10.1 The main evaluation indicators**

Time to recurrence (TTR): the time between the date of surgery and being found recurrence by examination. In case patients are lost to follow, or with unexplained death, TTR are calculated until this point.

Recurrence: new intrahepatic lesions are found in abdominal CT or MRI with the typical characteristics of enhancement in arterial phase, degradation in portal and delayed phase; chest X-ray finds lung metastasis which should be confirmed by lung CT; If there are any symptoms of adrenal gland, bone, intracranial and other metastasis, abdominal CT, bone scan, and other relative examinations should be used as diagnosis.

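### Section 13.2 fixes a pretest-gated t test for continuous markers, with no baseline covariate and no method if a pretest fails; ANCOVA on values already collected would do better (minor)

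*Protocol*

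**What the plan says.** Section 13.2 gives one rule for all continuous data: the comparison between groups "took use of t test after normal step test and homogeneity test for variance". It mentions no covariate or transformation, and no method for data that fail either pretest. The same section makes all tests two-sided at 0.05 and says that a statistical analysis plan will follow.

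The data come from two places:

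- Section 4.3: "All of the patients will receive venous blood collection on one day before surgeries and day 7 after surgery". Aminotransferase and bilirubin are measured; also "AFP and MMP-9 will be measured via radioimmunoassay", and "activity of nature killer cells and T cell subsets will be measured by flow cytometers".
- Section 8.1 lists among the entry examinations "Serum tumor markers: AFP, CEA, and CA199". Section 8.2 repeats tumour markers during follow-up, at intervals of two to three months.

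The heading of section 10 states that "the judgment of efficacy is mainly based on the following indicators". Time to recurrence is then the main indicator (10.1), and overall survival and survival rates are secondary (10.2). Section 10.3 adds only that "the changes of tumor markers will be evaluated", without a method.

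**The concern.** There are two weaknesses in the one sentence.

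First, the analysis is conditional on pretests but only one branch is written down. Tumour markers such as AFP may well be strongly skewed. If they are, the pretest fails and the test actually used is chosen after the data have been seen.

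Second, a t test makes at best partial use of the pre-operative value. Section 4.3 assigns patients to groups after the resection, so the sample from the day before cannot be affected by allocation and is a valid covariate. With 68 patients in all, leaving it out gives up precision and leaves the comparison open to chance baseline imbalance.

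At stake is the precision and pre-specification of the supporting marker and liver-function comparisons, not the trial's main conclusion.

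**Working it through.** **The plan's own figure.** The only design figure is N = 68 for time to recurrence (section 4.2: medians 18 and 36 months, HR 0.5, one-sided 0.05, power 0.80, five years of follow-up). Schoenfeld events: 4(1.645 + 0.842)²/(ln 0.5)² = 51.5, so 52. With exponential times, the event probability by 60 months is 1 − 0.5^(60/18) = 0.901 (control) and 1 − 0.5^(60/36) = 0.685 (treated), mean 0.793. Then 52/0.793 = 65.6, so 66, within two patients of 68. The figure reproduces, but it says nothing about markers: the protocol gives no SD, correlation or power for them.

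**Assumptions for the markers.** 34 per arm (68 split 1:1; the ratio is not stated), a true difference d = 0.5 SD, a near-normal scale, and a pre/post correlation ρ shown over a range. Two-sided 0.05 is from section 13.2.

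**Formulas.** Power comes from the noncentral t with noncentrality d/√(2v/34) = 2.06/√v, where

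- post-value t test: v = 1, 66 df;
- change-score t test: v = 2(1 − ρ), 66 df;
- ANCOVA: v = (1 − ρ²)(1 + 1/64), 65 df.

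Apart from the small-sample factor, the ANCOVA variance is 1 − ρ² of the post-value variance and (1 + ρ)/2 of the change-score variance. The gain therefore vanishes near ρ = 0 against the post value and near ρ = 1 against change.

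| ρ | Post value | Change: v, power | ANCOVA: v, power |
|---|---|---|---|
| 0 | 52.9% | 2.0, 30.1% | 1.016, 52.2% |
| 0.1 | 52.9% | 1.8, 32.8% | 1.005, 52.6% |
| 0.3 | 52.9% | 1.4, 40.4% | 0.924, 56.1% |
| 0.5 | 52.9% | 1.0, 52.9% | 0.762, 64.3% |
| 0.7 | 52.9% | 0.6, 74.6% | 0.518, 80.6% |
| 0.8 | 52.9% | 0.4, 89.5% | 0.366, 91.9% |

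Against the post-value test, ANCOVA gains 3, 11 and 28 points at ρ = 0.3, 0.5 and 0.7, and loses 0.7 and 0.3 points at ρ = 0 and 0.1. Against the change score it gains 16, 11 and 6 points at ρ = 0.3, 0.5 and 0.7. The difference detectable with 80% power is 0.69 SD for the post value, and 0.66, 0.60 and 0.50 SD for ANCOVA at ρ = 0.3, 0.5 and 0.7.

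**The pretest gate.** In simulation (2,000 trials per setting; Shapiro–Wilk in each arm plus Levene on the post value), the share of trials passing was 0% for a lognormal marker with log-SD 1.0, about 1% at log-SD 0.6, 30–33% at log-SD 0.3, and about 86% for normal data.

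**Separating scale from covariate.** For a lognormal marker with log-SD 1.0, ρ = 0.5 and a difference of 0.5 SD on the log scale, power was:

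- raw post-value t test 39%;
- raw change t test 37%;
- pretest, then t or Mann–Whitney on the post value 52% (Mann–Whitney is assumed, since the protocol names nothing);
- log post-value t test 54%;
- log ANCOVA 65%.

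The log scale accounts for 54 − 39 = 15 points and the covariate for a further 65 − 54 = 11.

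**Type I error.** Across all null settings and methods it lay between 3.2% and 6.3%.

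**The case against.** The strongest reply is that this belongs in the statistical analysis plan, which section 13.2 announces and which is not shown. Covariates, transformations and the fallback for non-normal data are commonly settled there, and the sentence in 13.2 assigns no test to any particular marker or visit. That limits the weight of the point. It does not remove it, because the protocol does not leave the method open: it states one for all continuous data, and a plan that follows it inherits the gap.

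Several stronger readings are tempting and are not supported:

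- *That the plan ignores baseline.* Section 13.2 does not say whether post values or changes are tested, and 10.3 speaks of changes, which do use baseline, only less efficiently than ANCOVA.
- *That the markers are key efficacy endpoints, given the heading of section 10.* They are neither the main nor the listed secondary indicators. The heading reaches only the tumour markers; MMP-9, the immune measures and liver function do not appear in section 10.
- *That liver injury from the implant could be missed.* Safety in section 11 rests on graded adverse events and serious-event reporting, not on a test of day-7 means.
- *That adjustment about doubles power.* With log-SD 1.0, ρ = 0.5 and a larger effect of 0.7 log-SD, a raw-change t test has about 40% and log ANCOVA about 90%. But that contrast mixes scale with covariate and assumes a treatment that lowers the marker. If treatment raises it, raw change has about 65%. A log post-value t test has about 81% and Mann–Whitney on the post value 79–80%, so adjustment itself adds roughly 10 points.

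The size of the gain is also uncertain. The tumour is removed between the two samples, and entry limits ALT and AST to twice the upper limit of normal, so low correlations are plausible. At ρ = 0 there is no gain over the post value.

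**Conclusion.** The point holds as a minor one. The firmer half is that the protocol prescribes a gated t test without saying what happens when the gate closes, which is near certain for a strongly skewed marker and does not depend on ρ. The other half is efficiency: under the stated assumptions ANCOVA gains 3 to 28 points of power over a post-value t test and 16 down to 6 points over a change score as ρ goes from 0.3 to 0.7, and costs less than 1 point against the post value at ρ of 0 to 0.1. The documents give neither the correlations nor the marker distributions, so these are ranges and not predictions.

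False-positive risk is not the issue, and the time-to-recurrence and survival analyses are untouched.

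**What to change.** In section 13.2, replace the t-test sentence with:

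> Continuous markers and liver function tests are compared between groups by ANCOVA with the pre-operative value of the same measure as covariate. Markedly skewed measures (e.g. AFP) are analysed on the log scale and reported as ratios of geometric means with 95% CI. No preliminary normality or variance test decides the method.

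Name the time point for each measure: day 7, or a stated follow-up visit for AFP, CEA and CA199, which are repeated. Keep logs for measures that are clearly skewed; nothing in the documents shows that they suit T-cell subsets or NK activity.

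The cost is a change of wording, with no new patients, samples or procedures. The downsides are one degree of freedom, a negligible loss of power if the correlation is near zero, and a ratio in place of a difference for the logged markers.
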